### Procedures to minimize bias

To minimize selection bias, randomization numbers will be assigned in strict sequence; that is, when a subject is confirmed as eligible for randomization, the next unassigned randomization number in sequence will be given. Permuted blocks will be used to generate the randomization assignments, in order to keep the balance of patients receiving each treatment assignment and help prevent the next treatment group from being discerned by site personnel. Randomization allocation will be concealed from the clinician and patient, using a centralized automatic web-based data management system.

Regarding assessment bias, due to the nature of the treatments, the study cannot be blinded (the form of SCS used in this trial requires paresthesia); however, to minimize potential assessment bias, questionnaires will be completed by patients without study staff consultation or visibility, using a secured electronic tablet.

To minimize attrition bias, if a subject misses a study visit the site’s study staff will make at least three documented attempts to bring that subject in for a study visit. The numbers and reasons for dropouts and losses to follow-up will be reported for each arm of the study.

To quantify potential performance bias, the level of OMM treatment and the addition/removal of SCS therapy for all participants at each follow-up to 24 months will be recorded. Additionally, we will compare changes in pain medication use and other healthcare utilization from baseline to the end of Period I for subjects in the SCS group with those in the OMM group. Any imbalance in OMM therapy between study arms will be considered in interpreting between-group outcome differences.

### Data analysis

#### **
*Statistical analysis*
**

For primary and secondary objectives, the primary analysis method will follow the intention-to-treat principle supported by completers’ and as-treated analyses. The following definitions will be applied: intention-to-treat analysis, between-group comparison based on random allocation of all subjects at the 6-month visit; completers’ analysis, between-group comparison based on random allocation of subjects with complete data at the 6-month visit; and as-treated analysis, between-group analysis based on the treatment subjects with complete data at the 6-month visit received at the 6-month visit.

The primary objective will be compared by *Z*-test using unpooled standard deviation with continuity correction, and a logistic regression model will be used for exploratory analysis. Secondary objectives will be assessed using linear regression models. To assess potential differences in treatment effect across sites, a treatment-by-site interaction term will be added to models. If the treatment-by-site interaction term approaches significance (defined as <0.10, as recommended by Fleiss [27]), the term will remain in the final model along with the term for site. In this case, the results for the objective will also be tabulated by site. Factors that might explain differences among sites will be explored.

There is no compelling evidence of patient-related (for example, age, sex) factors that predict the outcome of SCS; however, in order to identify baseline characteristics that might have predictive effects on outcomes, exploratory analysis with regression models may be conducted including baseline covariates. For the analysis of secondary objectives, baseline assessments for pain score and the Oswestry Disability Index will be included in the regression models as covariates.

Missing data are a potential source of bias. A rigorous study design and execution will help prevent the incidence of missing data from occurring. For the primary objective, patients with missing data at the end of Period I will be treated as nonresponders (failures). With this approach, we assume that nonresponders in both treatment groups have no change in their outcomes compared with baseline. This method has been chosen over more complex imputation methods, such as multiple imputation, because it has been empirically demonstrated in trials of chronic pain to produce conservative treatment effects [28]. For the secondary study objectives, no change from baseline will be assumed for patients with missing data. For completers’ and as-treated supporting analyses, only completers will be included in the analysis.

Period II is the long-term follow-up phase, which includes the possibility for patients to change from their original treatment assignment to the alternative treatment. The objectives of Period II are to compare within-patient changes (that is, baseline versus follow-up) in each group. Because the study design allows patients to change from the randomized treatment group to the alternative treatment after 6 months of follow-up, the analysis of objectives in Period II will be based on the treatment patients actually received and not on the randomization assignment. Only completers will be included.

Unadjusted *P* values will be reported. To maintain an overall type I error rate at 0.05, a fixed-sequence method for the multiplicity adjustment of hierarchical endpoints will be used to test the primary and secondary objectives. No multiplicity adjustment will be performed for evaluations of the additional study objectives. A validated statistical software package will be used for the analyses of the study results (for example, SAS, SPLUS). These analyses are detailed in a statistical analysis plan.

#### **
*Economic evaluation*
**

Economic analyses consider the costs and effectiveness of treatments. Costs will be calculated by multiplying units of healthcare use used by the cost of each unit. Effectiveness will be expressed as quality-adjusted life-years, with these data derived from patients’ responses to the EQ-5D-5 L.

A within-trial cost-consequence analysis will include a disaggregated report of costs and quality-adjusted life-years and of other health outcomes observed in the two groups at 6, 12, and 24 months [29]. Cost utility analysis modeling, extrapolated over a longer time horizon (that is, 15 years), will estimate the incremental cost per quality-adjusted life-year ratio for SCS and OMM. These analyses will be detailed later in a health economic analysis plan.

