### Aims and objectives

The PROMISE study is a RCT comparing the clinical effectiveness of SCS using the Specify® 5-6-5 surgical lead (Medtronic, Inc., Minneapolis, MN, USA) plus optimal medical management (OMM) versus OMM alone in patients suffering from predominant low back pain due to FBSS. After the 6-month visit, patients can change treatment to that received by the other randomized group. All patients will be followed for 24 months post randomization.

The primary objective is to determine the difference in the proportion of patients receiving SCS plus OMM versus the proportion receiving OMM alone who have ≥50% reduction in back pain intensity, as measured by the Numeric Pain Rating Scale (NPRS), from baseline to 6 months. Secondary objectives are to compare changes in the following outcomes from baseline to 6 months between the two groups: low back pain intensity, as measured by the NPRS [18]; leg pain intensity, as measured by the NPRS [18]; functional disability, as measured by the Oswestry Disability Index [19]; and quality of life, as measured by the Short-Form Health Survey, version 2 physical component summary score [20]. Additional objectives include the comparison of other patient-related outcomes and healthcare utilization including medication usage (see below) at 6 months, to assess within-patient changes (that is, compared with pre-randomization) in outcomes from 6 to 24 months post randomization, to characterize all SCS-related and non-SCS-related adverse events, and to assess the costs and cost-effectiveness of SCS plus OMM versus OMM alone.

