A patient is considered enrolled in the study upon completion of the informed consent process. Enrolled subjects will be taught how to complete a pain diary between the enrolment visit and the randomization visit. The subject will record his/her low back and leg pain scores during a 7-day pain diary period prior to randomization. Subjects will not be told what confirmatory pain scores are required for study inclusion. The inclusion criteria of average NPRS score to assess low back and leg pain will be evaluated after the subject completes the pain diary. Candidacy for SCS with the Specify® 5-6-5 implant will also be confirmed based on appropriate imaging according to usual practice. In addition, where a psychological evaluation (or other evaluation) is standard of care and/or required, the evaluation must take place prior to randomization. The principal investigator will document whether the patient has received the required evaluation and the results of that evaluation. FBSS diagnosis will also be confirmed based on appropriate imaging according to usual practice.

The principal investigator or his/her designee will review the diary to confirm that the pain intensity scores and pain location meet the inclusion/exclusion criteria (see above). In addition, the principal investigator will document that the patient is a candidate for implantation of a Specify® 5-6-5 SCS system. Upon confirmation of eligibility, OMM treatment planning and completion of the questionnaires, subjects will be randomized to one of the two treatment groups. Subjects who do not complete or meet preliminary eligibility requirements will not be randomized and will be exited from the study.

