### Assessments

Outcome measures selected for this trial are based on a review of the previous RCTs of SCS and a consideration of IMMPACT recommendations [18].

The day of randomization is day 0 for the study periods. Subjects will be assessed prior to randomization (baseline) and at 1-month, 3-month, 6-month, 9-month, 12-month, 18-month and 24-month follow-up visits. Visit windows for Period I and Period II will remain constant based on the original date from the randomization visit, regardless of whether any change in therapy occurs. Assessments will be performed by appropriately trained and delegated study staff according to the usual practices of the site. Electronic case report forms will be used for this study with patients completing the study questionnaires confidentially on electronic tablets, and these data will be uploaded to a web-based server. Table 1 provides a summary of the data collection process and timing.

**Table 1 T1:** PROMISE study – summary of data collection

**Study procedure**	**Enrollment**	**Randomization**	**Screening test**	**Implant**	**1 month**^ **a** ^	**3 months**^ **b** ^	**6 months**^ **b** ^	**9 months**^ **b** ^	**12 months**^ **b** ^	**18 months**^ **b** ^	**24 months**^ **b** ^	**Unscheduled**	**Early discontinue**^ **c** ^
Time window (days)	-90 to 0	0	0 to 57	3 to 60	10 to 67	68 to 137	138 to 228	229 to 319	320 to 455	456 to 637	638 to 789	NA	NA
Informed consent	**X**												
Demographics (age, gender)	**X**												
Medical history	**X**												
Inclusion/exclusion criteria	**X**	**X**											
Pain location	**X**	**X**											
Pain diary (complete prior to visit)		**X**			**X**	**X**	**X**	**X**	**X**	**X**	**X**		**X**
OMM treatment plan		**X**			**X**	**X**	**X**	**X**	**X**	**X**	**X**		
Questionnaires (ODI, SF-36, EQ-5D^d^, Pittsburgh Sleep Quality Index, employment status, pain and/or paresthesia map)		**X**				**X**	**X**	**X**	**X**	**X**	**X**		**X**
Randomization assignment		**X**											
Neuropathic pain (DN4)		**X**											
PGIC, Patient satisfaction with therapy						**X**	**X**	**X**	**X**	**X**	**X**		**X**
Nondrug pain treatment and other healthcare use assessment		**X**	**X**	**X**	**X**	**X**	**X**	**X**	**X**	**X**	**X**		**X**
Payer information (US only)	**X**								**X**		**X**		
Medication assessment		**X**	**X**	**X**	**X**	**X**	**X**	**X**	**X**	**X**	**X**		**X**
Event assessment^d^		**X**	**X**	**X**	**X**	**X**	**X**	**X**	**X**	**X**	**X**	**X**	**X**

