Screening test assessment			**X**										
Implant information			**X**	**X**									
Request for change in randomized therapy							**X**	**X**	**X**	**X**	**X**	**X**^ **e** ^	
SCS therapy thresholds							**X**						
Device interrogation (initial and final)				**X**^ **f** ^	**X**	**X**	**X**	**X**	**X**	**X**	**X**	**X**	**X**

DN4, Douleur neuropathique en 4 questions; ODI, Oswestry Disability Index; OMM, optimal medical management; PGIC, Patient Global Impression of Change; SF-36, Short-Form 36; SCS, spinal cord stimulation.

^a^For subjects randomized to SCS, the 1-month visit should occur a minimum of 7 days after implant (or screening test if the test was unsuccessful).

^**b**^Visits should occur within the window but at least 2 weeks after the previous visit.

^c^Early discontinuation, collect data if possible.

^d^When possible, collect additional EuroQoL (EQ-5D) at time of event if device-related event requiring surgical intervention or hospitalization occurred.

^e^Only after 6 months.

^f^No initial interrogation at implant, final only.

#### **
*Primary outcome*
**

The primary outcome is the proportion of subjects with ≥50% reduction in low back pain intensity measured using the NPRS at 6 months [18]. Pain relief will be assessed as a reduction of the 11-point NPRS. Patients will record their low back and leg pain using a (paper) pain diary two times per day, once in the morning and once in the evening, for a 7-day period within 2 weeks prior to the randomization visit and subsequent scheduled study visits. For the initial baseline pain diary, patients are required to complete at least 5 of 7 days in their entirety, or they will not proceed to randomization. The proportion of subjects in each group with ≥50% reduction in average low back pain score at the end of Period I compared with baseline will be calculated.

#### **
*Secondary outcomes*
**

Secondary outcomes are: Back and leg NPRS score [18]; Oswestry Disability Index version 2 [19]; and Physical Component Summary score on the Short-Form 36 [20].

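### The covariate list for the secondary models omits baseline SF-36 PCS, so the PCS comparison as written is unbiased but less precise than the collected data allow

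*Protocol article*

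**What the plan says.** The Aims and objectives section says the secondary objectives are to "compare changes in the following outcomes from baseline to 6 months between the two groups". It names four outcomes: back pain NPRS, leg pain NPRS, the Oswestry Disability Index (ODI), and "quality of life, as measured by the Short-Form Health Survey, version 2 physical component summary score". The Assessments section repeats the last of these as a secondary outcome: "Physical Component Summary score on the Short-Form 36".

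Under Data analysis, "Secondary objectives will be assessed using linear regression models", and for these models "baseline assessments for pain score and the Oswestry Disability Index will be included in the regression models as covariates". The same section says that "a fixed-sequence method for the multiplicity adjustment of hierarchical endpoints will be used to test the primary and secondary objectives", with the overall error rate held at 0.05. PCS is therefore part of the error-controlled family.

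Baseline PCS will exist. The row of Table 1 that begins "Questionnaires (ODI, SF-36, EQ-5D" is marked at the randomization visit, and the Selection of patients section puts the questionnaires before allocation: "Upon confirmation of eligibility, OMM treatment planning and completion of the questionnaires, subjects will be randomized to one of the two treatment groups".

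The only other mention of covariates concerns optional exploratory models that look for baseline predictors of outcome. It does not govern the secondary tests.

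**The concern.** The named covariates match the measures behind three of the four secondary outcomes (the two pain scores and ODI) and leave out the fourth. This is more than silence, because the article commits to a specific list and the list is incomplete for one of the outcomes it serves.

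A change score without its own baseline in the model fixes the slope of follow-up on baseline at 1. If the true slope is below 1, change is negatively related to baseline. Baseline variation in PCS then stays in the residual, and a chance difference in baseline PCS between the groups carries into the estimated effect. Baseline ODI and pain absorb only the part of this that they share with baseline PCS. What is at stake is the standard error of one secondary comparison, and how far its result depends on chance imbalance.

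**Working it through.** The article gives no power, standard deviation or correlation for PCS, so there is no stated figure to reproduce. The check compares the residual variance of the PCS model as written with that of the same model plus baseline PCS.

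**Inputs**
- From the article: change from baseline as the outcome; linear regression; baseline ODI in the model; 212 patients, 106 per group (a number set for the primary outcome).
- Assumed: correlation r between baseline and 6-month PCS of 0.4 to 0.7; correlation of size q between baseline PCS and baseline ODI (negative in sign) of 0.4 to 0.7; equal PCS variance at both times, scaled to 1; ODI related to 6-month PCS only through baseline PCS; baseline pain adding nothing further.

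**Formulas**
- Variance of change: 2(1 − r).
- Covariance of change with baseline ODI: −qr + q = q(1 − r).
- Residual variance as written (ODI only): 2(1 − r) − [q(1 − r)]².
- Residual variance with baseline PCS added: 1 − r². Once baseline is in the model, modelling the change or the 6-month score gives the same treatment effect.
- Reduction: 1 − (with PCS ÷ as written).

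**Results**

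| r | q | As written | With baseline PCS | Reduction |
|---|---|---|---|---|
| 0.4 | 0.4 | 1.2 − 0.24² = 1.142 | 0.840 | 26% |
| 0.4 | 0.7 | 1.2 − 0.42² = 1.024 | 0.840 | 18% |
| 0.5 | 0.4 | 1.0 − 0.20² = 0.960 | 0.750 | 22% |
| 0.5 | 0.7 | 1.0 − 0.35² = 0.878 | 0.750 | 15% |
| 0.6 | 0.4 | 0.8 − 0.16² = 0.774 | 0.640 | 17% |
| 0.6 | 0.7 | 0.8 − 0.28² = 0.722 | 0.640 | 11% |
| 0.7 | 0.4 | 0.6 − 0.12² = 0.586 | 0.510 | 13% |
| 0.7 | 0.7 | 0.6 − 0.21² = 0.556 | 0.510 | 8% |

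In patient terms, 212 patients analysed as written carry the information of about 156 (212 × 0.840/1.142) to 194 (212 × 0.510/0.556) analysed with baseline PCS.

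**Illustrative power.** Take r = 0.5, q = 0.6, an assumed effect of 0.4 SD and 106 per group. Residual variance is 1 − 0.30² = 0.91 as written and 0.75 with baseline PCS. Standard errors are √(2 × 0.91/106) = 0.131 and √(2 × 0.75/106) = 0.119. Power at two-sided 0.05 is 86% and 92%.

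**Bias check.** A 2,000-run simulation at the same r and q, with a true effect of 0.40, gave mean estimates of 0.402 under both models. Empirical standard errors were 0.131 and 0.118, a variance ratio of 1.23 (formula: 0.91/0.75 = 1.21). The models differ in precision, not in expectation.

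**Effect of the missing-data rule.** The article assumes no change from baseline for missing secondary data, which raises the effective correlation. With an assumed 15% missing at random, r = 0.5 becomes 0.85 × 0.5 + 0.15 = 0.575. At q = 0.7 the residual variances are 0.85 − (0.7 × 0.425)² = 0.761 and 1 − 0.575² = 0.669. The reduction falls from about 15% to about 12%.

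**The case against.** The strongest reply is that the sentence does not say that only pain and ODI are included, that the article refers to a separate statistical analysis plan, and that full covariate lists by endpoint usually sit there. This stands in part: the unseen plan may add baseline PCS, and a reader should not infer that PCS will certainly go unadjusted. It does not remove the point, because the article gives a definite list and following that list gives the less precise analysis.

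The second reply is that the harm is modest, and this stands in full. A reader might infer that the omission biases the PCS result through regression to the mean, or threatens the error control of the fixed sequence. The documents do not support either inference. Under 1:1 randomization, regression to the mean affects both groups equally in expectation, baseline is already subtracted in the change score, and the test keeps its level. Nor can one say that a failed PCS test would block later tests, because the article does not give the testing order; if it follows the order of the Aims section, PCS comes last.

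The third reply concerns size. One could suppose that each model carries only its own baseline, so that the PCS model has no covariate at all. The ratio would then be (1 + r)/2, a reduction of 30% at r = 0.4 and 20% at r = 0.6. The sentence, however, places pain and ODI in the secondary models generally, so these larger figures should not be used. Baseline pain, ignored in the calculation, would probably recover a little more of the loss. The trial was not sized on PCS, and the primary Z-test is untouched.

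**Conclusion.** The point holds as one of precision. As the article is written, the error-controlled comparison of PCS change is not adjusted for baseline PCS, although that baseline is collected before randomization. The comparison remains valid. It is less precise than it need be, and more exposed to chance imbalance in baseline PCS than baseline ODI and pain can correct.

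On the stated assumptions, adding baseline PCS cuts residual variance by roughly 8 to 26%. Equivalently, the standard error as written is about 4 to 17% larger (√(0.556/0.510) to √(1.142/0.840)). The gain is smallest where both correlations are high, and it shrinks further if many values are imputed as no change. It is positive throughout the assumed range. None of these correlations comes from the document, so the figures show the order of magnitude and do not estimate the loss in this trial.

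**What to change.** Replace the covariate sentence under Data analysis with a statement that each secondary outcome is analysed by linear regression with its own baseline value as a covariate (back NPRS, leg NPRS, ODI and, in the PCS model, SF-36 PCS), in addition to the covariates already listed. If the statistical analysis plan already does this, the two documents only need to say the same thing.

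The cost is one sentence. No data, visits or patients are added. The change should be made before any comparative PCS results are seen, because a covariate added to a confirmatory model afterwards could look data-driven.

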### Ethics and governance

Each investigation site’s Ethics Committee/Institutional Review Board (EC/IRB) will be required to approve the clinical investigational plan (CIP), the written patient information and consent form, any other written information to be provided to the patients, and, if applicable, product labeling and materials used to recruit patients. EC/IRB approval of the study must be provided in the form of a letter before commencement of the study at the investigation site. Site EC/IRB approvals at the time of submission (3 July 2013) of this protocol are listed in Additional file 2.

Each principal investigator will ensure that no study-related activities occur prior to EC/IRB approval and will provide adequate oversight to ensure that the study is conducted in accordance with the outlined standards. Study conduct will be in accordance with the ethical principles that have their origin in the latest version of the World Medical Association Declaration of Helsinki – Ethical Principles for Medical Research Involving Human Subjects (October 2008), Clinical Investigation of Medical Devices for Human Subjects – Good Clinical Practice (International Organization for Standardization 14155:2011) [30] and the laws and regulations of the countries in which the study is conducted (including data protection laws) and the requirements of the study CIP.

Prior to site initiation or subsequent involvement in study activities, the sponsor will provide study training relevant and pertinent to the personnel conducting study activities, including investigator responsibilities and device training (for example, study recommendations for implant procedures and programming, and the requirements of the CIP, informed consent process, and case report forms). Study-specific training will be documented prior to site initiation.

Monitoring visits will be conducted periodically according to the requirements of the study monitoring plan. The monitoring plan will also define source data to be directly recorded on the electronic clinical report form. This information will be provided to the site during site initiation. After site initiation and training, monitoring visits will be conducted periodically to assess site study progress, the investigator’s adherence to the CIP, regulatory compliance (including but not limited to EC/IRB approval and review of the study), maintenance of records and reports, and review of source documents against patient electronic clinical report forms. Monitors will facilitate site regulatory and study compliance by identifying any findings of noncompliance and communicating those findings along with recommendations for preventative/corrective actions to site personnel. Monitors may work with study personnel to determine and recommend appropriate corrective action(s) and to identify trends within the study or at a particular site.

